***Primary outcome***		
Outcome 1	Hospital admissions ≤ 30 days	Proportion of hospital admissions within 30 days follow-up (Day 0^a^ to Day 30)
***Secondary outcomes***		
Outcome 2	Hospital admissions at Day 0^a^	Proportion of hospital admission at Day 0^a^
Outcome 3	Readmission ≤ 30 days	Proportion of readmissions within 30 days follow-up (Day 1 to Day 30)
Outcome 4	Mortality ≤ 30 days	Number of deaths within 30 days follow-up (Day 0^a^ to Day 30)
Outcome 5	Length of hospital admission	Number of days admitted
Outcome 6	Hospital-free days ≤ 30 days	Number of days alive that is spend outside of an acute-care hospital, long-term acute-care hospital or in an emergency department. Days spent wholly or in part under “observation” status counts as hospital days [44]
Outcome 7	Complications during hospital admission	Number of complications during admission, registered in the electronic patient journal
Outcome 8	Treatment initiations or changes at Day 0^a^	Number of treatment initiations or changes at Day 0^a^
Outcome 9	Treatment initiation or changes ≤ 30 day	Number of treatment initiations or changes within 30 days follow-up (Day 1 to Day 30)
Outcome 10	Functional level	Proxy assessment of functional level: - Change in amount of home care within 30 days follow-up - Number of changes of dwelling
Outcome 11	Re-referrals to the ACHCS	Number of re-referrals to the ACHCS
Outcome 12	Contact to the PCP ≤ 30 days	Number of contacts to the PCP within 30 days follow-up (Day 0^a^ to Day 30)

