### Data analyses

#### Sample size and statistical power

A parallel group design with a 1:1 allocation ratio and a superiority design was chosen for this trial. To our knowledge, the number of patients acutely admitted after a visit from ACNs are unknown. Preliminary results from a pilot-study of the intervention (not yet published) showed that 21% of included participants were acutely admitted after a visit from ACNs. We aimed to detect a clinically significant absolute reduction in acute hospital admission of 10%. Therefore, based on data from the unpublished pilot-study, we aimed in detecting a reduction from 31 to 21% at a significance level 0.05 with a power of 0.80, requiring a total of 602 participants (301 in each arm). Allowing for a 5% dropout after randomisation, 316 in each arm are required (a total of 632 participants).

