### Over-diagnosing and over-treatment

We hypothesize that extended POCT improves the bedside diagnostic process and qualifies PCPs’ clinical decision-making on treatment, thereby reducing hospital admissions. However, the intervention could lead to an increase in hospital admissions by identifying conditions and diseases requiring further investigations or therapeutic treatment at hospital. We believe that by identifying conditions and diseases earlier, factors such as hospital length of stay, amount of home care, and functional status can be positively influenced during the 30 days follow up, as the patients are admitted prior to functional decline.

Any diagnostic test has false positive results, and both FLUS and bedside blood-analysis have false positive or inconclusive results that can lead to unnecessary additional treatments and hospital admissions.

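### Length of stay, complications and readmission are worded around an admission, with no value for participants never admitted and no index discharge for readmission, which invites a comparison selected on the primary outcome

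*Protocol article*

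**What the plan says.** All places are in the protocol article.

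- **Primary outcome (Table 1):** "Proportion of hospital admissions within 30 days follow-up (Day 0^a^ to Day 30"), with Day 0 the day of inclusion.
- **Outcome 3, readmission (Table 1):** "Proportion of readmissions within 30 days follow-up (Day 1 to Day 30"). The row mentions neither an earlier admission nor a discharge.
- **Outcome 5, length of admission (Table 1):** "Number of days admitted". The row has no time window and no value for the never-admitted. The Background and the column heading of Table 2 point to 30 days, but nothing says how a stay running past Day 30 is counted.
- **Outcome 7, complications (Table 1):** "Number of complications during admission, registered in the electronic patient journal". Again there is no value for the never-admitted.
- **Outcome 6, hospital-free days (Table 1):** days alive and out of hospital within 30 days, which every participant has.
- **Statistical analyses:** intention-to-treat, among eligible participants whose outcome data are available. Secondary outcomes are compared between the two groups by logistic regression.
- **Over-diagnosing and over-treatment (Discussion):** "We believe that by identifying conditions and diseases earlier, factors such as hospital length of stay" can be improved. The reason given is that patients reach hospital before their function declines. The same section accepts that the intervention could instead raise admissions.

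**The concern.** Whether a participant is admitted is decided after randomisation, and changing it is the purpose of the intervention. If length of stay and complications are compared only among the admitted, the two admitted groups are selected differently by treatment, and randomisation no longer protects the comparison. If the intervention keeps the milder cases at home, the patients still admitted are sicker on average, and stay and complications per admission rise with no harm done. If it keeps the more severe cases at home, the same comparison shows a benefit per admission that is only selection.

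The wording leans towards that analysis. A person never admitted has no length of admission in the ordinary sense, and an analysis set defined by available outcome data may then drop that person. The Discussion argues about stay in terms of patients who are admitted.

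Readmission has a fault of definition. Its window starts the day after inclusion, not at a discharge. A participant first admitted on Day 5 falls inside it, although that is no readmission.

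**Working it through.** **Step 1. Reproduce the planned figure.** The sample size section states "we aimed in detecting a reduction from 31 to 21% at a significance level 0.05 with a power of 0.80" and 301 per arm. With a two-sided test (sidedness is not stated) and pooled variance, p̄ = (0.31 + 0.21)/2 = 0.26:

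n = [1.96·√(2·0.26·0.74) + 0.842·√(0.31·0.69 + 0.21·0.79)]² / 0.10² ≈ 300.9, rounded up to 301 per arm (602 in total). This matches, so 31% and 21% can be used as planning rates.

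**Step 2. Size of the admitted groups.**

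- Control: 0.31 × 301 = 93.3, about 93.
- Intervention: 0.21 × 301 = 63.2, about 63.

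Assume nobody is admitted only because of the intervention. Then 21% are admitted in either arm and 10% only under control. So 10/31 = 32% of admitted controls have no counterpart among the admitted in the other arm.

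**Step 3. What an admitted-only comparison would show.** Let s be the mean outcome of those admitted in either arm and m the mean of those admitted only under control. The intervention has no other effect.

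- Control, among admitted: (0.21s + 0.10m)/0.31. Intervention, among admitted: s.
- Difference among admitted: (0.10/0.31)(s − m).
- Difference over all randomised, zero if never admitted: 0.21s − (0.21s + 0.10m) = −0.10m.

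The article gives no stay or complication figures, so s and m are assumptions. For mean stay in days:

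| s, m | Among admitted: control vs intervention | Difference | All randomised: control vs intervention | Difference |
|---|---|---|---|---|
| 8, 2 | 6.06 vs 8.00 | +1.94 | 1.88 vs 1.68 | −0.20 |
| 6, 3 | 5.03 vs 6.00 | +0.97 | 1.56 vs 1.26 | −0.30 |
| 6, 6 | 6.00 vs 6.00 | 0 | 1.86 vs 1.26 | −0.60 |
| 6, 8 | 6.65 vs 6.00 | −0.65 | 2.06 vs 1.26 | −0.80 |

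Complications follow the same pattern. With assumed risks of 30% and 10%, they are 23.5% vs 30% among the admitted and 7.3% vs 6.3% over all randomised.

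The sign among the admitted depends only on whether the averted admissions are milder or more severe than the rest. For the first row, with an assumed SD of 5 days, SE = 5·√(1/93 + 1/63) = 0.816 and z = 1.935/0.816 = 2.37. The chance of a significant, spuriously longer stay is about 66%; with an SD of 7 days it is about 40%. This is a comparison of means, used to show the selection. It is not the model the article names.

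**Step 4. Readmission, by reading the windows together.** The primary outcome covers Day 0 to Day 30, outcome 2 covers Day 0, and outcome 3 covers Day 1 to Day 30. Outcomes 2 and 3 therefore split the primary window. There are two readings:

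- *Any admission in Day 1 to Day 30 counts.* Every participant can then score, so there is no selection, but first admissions are labelled readmissions and the outcome overlaps the primary.
- *A prior admission is required.* The label is then right, but if the denominator is the admitted, the selection of Step 3 applies. With assumed readmission risks of 25% and 10%, it is 20.2% vs 25% among the admitted, and 6.25% vs 5.25% over all randomised.

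Each reading has one of the two faults, and the text does not choose between them.

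**The case against.** The strongest reply is that no sentence restricts these outcomes to admitted participants. Days admitted and number of complications are counts, and a never-admitted participant can score zero. The article commits to intention-to-treat and to comparing the two groups. Admissions come from the hospital record and national registers, so zero days is known, not missing. The analysis plan is not shown and could state the denominator. Hospital-free days already gives a measure of hospital time free of this selection.

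Most of that stands. A reader might infer that the plan commits to an admitted-only comparison, or that a successful intervention will look harmful. The documents support neither. The denominator is open, and the direction depends on who is kept out of hospital: the bias is nil with no severity contrast and favours the intervention if the averted cases are the more severe. Nor does length of stay carry the primary hypothesis, which concerns admission alone. A reader might also fault outcome 3 for leaving someone discharged on Day 27 only 3 days at risk. A fixed window from inclusion keeps the randomised comparison, and that short period is no fault once everyone randomised is counted.

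The reply does not remove the problem in the definitions. Table 1 is where the article defines its outcomes. The readmission row as written admits first admissions. Outcome 6 does not repair outcomes 3, 5 and 7, which remain listed for comparison between arms. In an open-label trial, two readings that can give opposite answers from the same data should not be left open.

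**Conclusion.** The point holds as a matter of definition. Outcomes 5 and 7 are worded for admitted participants with no value for the rest, outcome 5 has no window in its row, and outcome 3 has no index discharge. Read as an admitted-only analysis, they would compare about 93 with 63 participants selected on the primary outcome, and about a third of the admitted controls would have no counterpart. That fraction rests on the planned rates and on nobody being admitted only because of the intervention.

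Under the assumed severities, the bias in mean stay runs from −0.65 to +1.94 days, whereas the all-randomised difference favours the intervention throughout. These are illustrations, since the article gives no stay or complication figures. Only secondary outcomes are touched. The primary analysis and the 301 per arm are unaffected.

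**What to change.** Reword the three definitions so that arms are compared over all randomised participants for Day 0 to Day 30.

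- **Outcome 5:** total hospital days in the window, 0 if never admitted. Read it alongside mortality and hospital-free days, because an early death outside hospital would otherwise score as a good result.
- **Outcome 7:** participants with any in-hospital complication, none if never admitted.
- **Outcome 3:** a second acute admission after a discharge, counted over all randomised participants.
- **Outcome 6:** name hospital-free days as the main between-arm measure of hospital time. It is already defined for everyone and counts death against the arm in which it occurs.
- **Per-admission figures:** report them descriptively, without a test between arms.

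The data are already being collected, so the cost is the wording of three definitions and the denominator in the analysis code. The downside is that per-admission comparisons become descriptive.

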Point-of-care ultrasound (POCUS) has become a diagnostic tool for acute respiratory diseases over the last couple of decades. Studies have shown, that in the hands of a trained health-professional, focused lung ultrasound (FLUS), is an accurate tool for diagnosing pulmonary oedema, pneumothorax, pleural effusion, and pneumonia in emergency departments and intensive care units. [23–25]. However, there is no knowledge about its use and effects on the diagnostic process during in-home assessments. Only few studies have investigated FLUS as a diagnostic tool for pneumonia in primary care, but these studies were not representative for the geriatric population [26, 27].

The objective of this trial is to investigate whether extended POCT, including FLUS and bedside blood analysis, during in-home assessments among older adults with signs of potential acute respiratory disease, reduces hospital admission. Our primary hypothesis is that implementation of extended POCT in this context will result in a reduction in hospital admissions within 30 days compared to individuals receiving usual care, constituting our primary outcome. Additionally, we anticipate that the extended POCT will improve the accuracy and timeliness of bedside diagnostics, leading to enhanced clinical decision-making by primary care physician – reflecting our secondary outcomes and tertiary outcomes. Finally, we hypothesize that the intervention will lead to earlier identification of conditions and diseases, subsequently influencing factors such as hospital length of stay, amount of home care, and functional status during the 30 days follow up. This early diagnosis is expected to prevent functional decline, aligning with our secondary outcomes.

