### Recruitment and enrolment

Patients referred to the ACHCS are visited by an ACN in their own dwelling, which may include a private house, care-home, or rehabilitation centre. If the patient fulfils the inclusion criteria, the ACN provides comprehensive information about the study both orally and in writing. Subsequently, the patient is given the opportunity to sign the informed consent document. Additional files 1 and 2 contain details pertaining to the informed consent process and written participant information. These documents have received approval from the Regional Committees on Health Research Ethics for Southern Denmark.

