### Outcomes

The primary outcome of this trial is the rate of hospital admission within 30-days follow-up. Secondary outcomes, along with their definitions, are listed in Table 1. The tertiary outcome involves evaluating ACNs diagnostic accuracy in conducting FLUS compared with a FLUS-specialist. A FLUS specialist will perform blinded assessment of all FLUS video clips. Outcome measures will include sensitivity and specificity, PPV and NPV, with a Bland-Altmann analysis. The results of the tertiary outcome will be reported in a separate paper.

**Table 1 Tab1:** Primary, secondary, and tertiary outcomes

	**Outcome**	**Outcome measure**

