**Secondary outcomes**							
Readmission					x		x
Death					x		x
Hospital-free days							x
Length of hospital stay					x		x
Complications during hospital stay					x		
Treatment initiations	x					x	x
Treatment changes						x	x
Amount of home care		x		x			
Re-referral to ACHCS				x			
Contact to PCP			x				x
*Data collector*	*ACN*	*Nexus administrator*	*Primary investigator*	*Nexus administrator and ACNs*	*Primary investigator*	*Primary investigator and ACNs*	*Primary investigator*

*ESCR* Electronic social care record, *EPJ* Electronic patient journal, *FMK* Medical chart (Fælles medicinkort)

^a^Day 0: Defined by Day of inclusion

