### Data sources

We will apply for access to external data sources to assess co-morbidity, disabilities, utilization of primary care and health care services, death, and medical history.

The Danish Health Data Authority is responsible for the national health registers containing health data related to all Danish citizens [46, 47]. A unique personal identification number for all people living in Denmark makes it possible to link data across national health registers. Approval granted August 2023.

The Danish Health Data Authority will be applied to get access to the Danish National Patient Registry, the Cause of Death Register, The Register of Pharmaceutical Sales, and the Danish National Health Service Register. The registers contain information about diagnoses, treatments, deaths, and health care utilization, and are needed to access information on comorbidity, time of death, medical history, treatment initiations or changes, and number of consultations at PCPs.

The Medical Chart (FMK: Fælles MedicinKort), will be applied to access register polypharmacy and type of medications. Data on amount and type of medication will be obtained at day 0 by the primary investigator. Treatment initiations or changes within 30 days follow-up (Day 1 to day 30) will be obtained by the primary investigator on Day 30. Approval granted October 2022.

The Municipal journal record, Electronic Social Care Record (ESCR), registers home care, and data will be obtained at day 1 and at day 30 to investigate possible changes as a proxy of changes in functional level. Approval granted October 2022.

The hospital journal record, EPJ will be accessed by the primary investigator to register admissions, reason for admission, and complications during admission. EPJ will be accessed at day 30 after the acute visit. Approval granted October 2022.

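### Outcome 10's dwelling component is an undirected count of moves, so a group difference in it cannot be read as better or worse function

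*Protocol article*

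**What the plan says.** The Outcomes section makes Table 1 the place of definition: "Secondary outcomes, along with their definitions, are listed in Table 1". There, Outcome 10 is a "Proxy assessment of functional level" with two components: "Change in amount of home care within 30 days follow-up" and "Number of changes of dwelling". Nothing in the article sorts moves by where they start or end.

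Under Recruitment and enrolment, patients are visited in their own dwelling, "which may include a private house, care-home, or rehabilitation centre".

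The Background gives the functional outcomes a purpose with a direction: "This early diagnosis is expected to prevent functional decline, aligning with our secondary outcomes".

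On sources, the Data collection section says Table 2 covers every outcome. For function, Table 2 has a row for the amount of home care and none for dwelling. The Data sources section describes the municipal care record as registering home care, and says "data will be obtained at day 1 and at day 30 to investigate possible changes as a proxy of changes in functional level". Dwelling is not mentioned there.

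**The concern.** A proxy for functional level has to move one way when function improves and the other way when it worsens. A count of moves does not do so in this population. Someone enrolled in a rehabilitation centre who recovers and goes home adds one. Someone enrolled at home who loses independence and enters a care home also adds one. A resident already in a care home has little room left to move towards more care.

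What is at stake is the interpretation of this component. The trial hopes to show that earlier diagnosis prevents decline. If the intervention speeds returns home and also reduces care-home entries, the two effects push the count in opposite directions. A null result could hide a benefit, and neither a higher nor a lower count would say which kind of move produced it.

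**Working it through.** The article gives no figure for Outcome 10, so there is none to reproduce. The check is mainly a reading of the definition, followed by illustrations whose rates are all assumed.

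**Step 1: the definition followed exactly.**

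| Move during follow-up | Natural reading | Adds to the count |
|---|---|---|
| Rehabilitation centre to home | recovery | 1 |
| Home to care home | decline | 1 |

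The enrolment settings make both rows possible. No section of the article separates them.

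**Step 2: why effects can cancel.** Let *m* be the proportion who move to more care and *l* the proportion who move to less care, with at most one move per person. The count per participant is *m* + *l*, so the group difference is Δ*m* + Δ*l*. If the intervention works, Δ*m* is negative and Δ*l* is positive. The difference is zero whenever the two are equal in size.

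**Step 3: illustrations (assumed rates).**

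- Cancellation: control *m* = 5%, *l* = 5%; intervention *m* = 2%, *l* = 8%. The totals are 10% and 10%, although moves to more care fall by 3 points.
- Higher total despite benefit: control *m* = 6%, *l* = 3%; intervention *m* = 4%, *l* = 8%. The totals are 9% and 12%, although moves to more care fall by 2 points.

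**Step 4: dependence on the share enrolled in rehabilitation centres (assumed rates).** Let *r* be that share. Suppose 40% of them go home under control, and 3% (control) against 2% (intervention) of everyone else move to more care.

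Count per participant: control = 0.40*r* + 0.03(1 − *r*); intervention = *h*·*r* + 0.02(1 − *r*), where *h* is the proportion going home under the intervention.

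| *r* | *h* | Control | Intervention |
|---|---|---|---|
| 5% | 60% | 0.0200 + 0.0285 = 0.0485 | 0.0300 + 0.0190 = 0.0490 |
| 10% | 60% | 0.040 + 0.027 = 0.067 | 0.060 + 0.018 = 0.078 |
| 20% | 60% | 0.080 + 0.024 = 0.104 | 0.120 + 0.016 = 0.136 |
| 10% | 45% | 0.040 + 0.027 = 0.067 | 0.045 + 0.018 = 0.063 |

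In every row both kinds of move favour the intervention. The total is nearly equal in the first row, higher under the intervention in the second and third, and lower in the fourth. The totals are equal when *r*(*h* − 0.40) = 0.01(1 − *r*), that is, *r* = 0.01/(*h* − 0.40 + 0.01). This gives 0.01/0.21 = 4.8% for *h* = 60%, and 0.01/0.06 = 16.7% for *h* = 45%.

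The sign of the difference in the total therefore depends on quantities the article does not give. In no row does the total identify which kind of move produced it.

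**Step 5: source.** Table 2 and the description of the municipal record both cover home care only. If dwelling were taken from the same two readings, at day 1 and day 30, a move out and back between them would not be seen. A count of all moves might then not be obtainable.

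**The case against.** The strongest reply is that this is coding detail. Table 1 names the measure in a few words, and a full protocol or analysis plan, not shown here, may say which moves count and how they are grouped. That would be decisive if the complaint were a missing rule. It is not: the article says Table 1 holds the definitions, and the measure printed there is a count that works badly as a functional proxy.

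Several further points stand and limit the finding:

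- A reader might infer that the plan treats more moves as worse function, so that recovery will be reported as decline. No section says so. The supported statement is that the count has no direction at all.
- A reader might infer from Step 4 that the intervention would look about 16% worse (0.078/0.067 = 1.16). That result needs an assumed 20-point gain in returns home, set against a 1-point fall in moves to more care. With a 5-point gain at the same 10% share, the total falls from 0.067 to 0.063. Reversal is possible but has not been shown to be likely.
- A reader might infer that the functional hypothesis cannot be tested. The home-care component can carry a sign, and it is the one the Data sources section names as the proxy for functional change. It is untouched.
- Whether each leg of a temporary stay counts is not stated, so no claim is made that a short rehabilitation stay outweighs a permanent move.
- The missing Table 2 row is a separate reporting gap. It does not bear on direction.

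**Conclusion.** The point holds in a limited form. As defined, the dwelling component adds moves towards less care and moves towards more care with equal weight. A between-group difference in it supports no conclusion about function, and a null difference can conceal real effects. This rests on two facts in the article: the measure is a bare count, and the places of enrolment allow moves in both directions. It does not rest on any assumed rate.

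The size of the distortion is unknown, because the article gives neither move rates nor the share of participants in rehabilitation centres. The scope is one of two components of one of eleven secondary outcomes (Outcomes 2 to 12). It is worth correcting because the remedy is cheap, but it does not threaten the trial's main result.

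**What to change.** - Classify each move by origin and destination. Place of assessment is already recorded at the home visit and gives the origin.
- Report two proportions: those living at a higher level of care at Day 30 than at inclusion, and, separately, those at a lower level. Each is binary and so fits the logistic regression planned for secondary outcomes.
- The sponsor should set the ordering of dwelling types, and the handling of temporary rehabilitation stays and of deaths before Day 30, before the groups are compared.
- Add dwelling to Table 2 with time points and a source that the sponsor confirms records it. The article does not show that the municipal record does.
- If the outcome is already fixed, which is plausible since inclusion was expected to end on 31 August 2023, keep the count and add the split by direction. Label the split as a change to the prespecified measure, and draw no functional conclusion from the total.

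The cost is a small amount of extra coding, one added table row and a documented outcome amendment. Moves have to be identified anyway in order to be counted. If the confirmed source turns out not to hold destination, the cost would be higher.

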### Study setting

The trial is conducted in Kolding Municipality, Denmark, covering an area of 604.5 km^2^ with a population of 93,161 people, of whom 18,453 are aged 65 years or older [29].

In 2018, it was enforced to all Danish municipalities to establish an Acute Community-based Health Care Service (ACHCS) to enhance the timely recognition of acute disease [30]. While municipalities had the freedom to organise the ACHCS, most introduced an outgoing function from community healthcare centres, operated by Acute community nurses (ACNs).

The ACHCS in Kolding Municipality has a stationary function and an outgoing function, with ACNs dedicated to the outgoing function. The ACNs conduct in-home assessments primarily for older vulnerable citizens with acute signs of health deterioration. Approximately 5 – 8 patients are referred daily for in-home assessment due to suspected emerging acute disease. Referrals are mainly made by PCPs, but hospital physicians and home care personnel also have the capability to make referrals. If home care personnel refer patients, the PCP will be notified and responsible for diagnosis and treatment.

The assessment of acutely ill patients includes a clinical assessment, objective vital status parameters (oxygen level, respiration frequency, pulse, blood pressure, temperature), and, when appropriate, on-site POCT for biochemical analyses, e.g., CRP and haemoglobin. All results are communicated to the PCP or the hospital physician, providing them with clinical, objective information that qualifies diagnosis and medical decision-making.

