### Intervention and control

In the control group, the ACN will carry out usual care, which involves a clinical inspection, measurements of vital signs (respiratory rate(breaths/min), saturation (%), blood pressure (mmHg), heart rate (beats/min), body temperature (C^0^), and Glasgow Coma Scale [36]), and POCT for CRP and haemoglobin.

The intervention group will receive extended POCT in addition to usual care. Extended POCT includes a FLUS and biochemical blood analyses. Biochemical blood analyses include sodium, potassium, creatinine, urea, and leucocytes with differential count.

In both control and intervention groups, the ACN communicates the examination results to the participants’ PCP through telephone communication and electronic message (EdiFact) for written documentation. The communication to the PCP is part of usual care and is carried out in both groups.

Preceding to commencement of the study, all ACNs undergo comprehensive training in FLUS, technical procedure of POCT biochemical blood-analysis, as well as training in research methods with a specific emphasis on study procedures. This training is designed to enhance their adherence to and compliance with the randomization procedure and protocol.

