***Tertiary outcomes***		
Outcome 14	ACNs diagnostic accuracy for conducting FLUS compared with a FLUS-specialist	ACNs conclusions are index test and FLUS-specialist conclusions used as reference test

*ACNs* Acute community Nurses, *ACHCS* Acute Community Health Care Service, *FLUS* Focused Lung Ultrasound, *PCP* Primary Care Physician

^a^Day 0: Defined by Day of inclusion

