### Statistical analyses

Statistical analysis will be carried out using STATA® (StataCorp LLC, Texas, USA).

Data analysis will be conducted according to intention to-treat principles and include all eligible participants with available outcome data. Missing data will be reported for each variables, including reasons. Imputation and sensitivity analysis will be used to assess the potential biases caused by missing outcome data.

Descriptive statistics for both groups will be summarised including demographic and baseline characteristics: patient symptoms, referring health professional, Clinical Frailty Scale (CFS) [45, 48], co-morbidities, daily medication, amount of home care, alcohol consumption, smoking, BMI, vital signs (blood pressure, pulse, oxygen saturation, respiratory frequency, and ear temperature), treatment initiations or changes, admissions, re-referrals to the ACNs, contacts to the PCPs, and mortality.

In the intervention group, descriptive statistics will also include POCT measurements and FLUS findings.

Categorical data will be reported as numbers and percentages. Continuous data will be presented as means (SD) on normally distributed data and medians [IQR] with range on non-normally distributed data. Differences in baseline characteristics between the intervention group and control group will be calculated using Chi-squared test, Fischer’s exact test, and Wilcoxon-Mann–Whitney test as appropriate. The statistical significance threshold for all tests is *p* < 0.05.

For the primary outcome univariate and multivariate logistics regression models will be used to investigate risk of admission between groups.

Univariate and multivariate logistic regression models will be used to compare secondary outcomes between the two groups.

Both regression models will be adjusted for possible confounders (gender, age, civil status, co-morbidity, alcohol consumption, smoking, living alone, and BMI).

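### Outcome 12 counts PCP contacts from the day of inclusion with no rule for contacts that allocation cannot change, and the stated logistic model does not fit a count

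*Protocol article*

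**What the plan says.** - **Definition.** Protocol article, Outcomes, Table 1: Outcome 12 is the "Number of contacts to the PCP within 30 days follow-up", with a window from Day 0 to Day 30. The table footnote reads "Day 0: Defined by Day of inclusion", so the window opens on a calendar day and not at the moment of randomisation.
- **Report of results.** Under Intervention and control, the nurse passes the findings to the PCP by telephone and electronic message: "The communication to the PCP is part of usual care and is carried out in both groups". Study setting is slightly wider: "All results are communicated to the PCP or the hospital physician".
- **Referral.** Study setting: "Referrals are mainly made by PCPs, but hospital physicians and home care personnel also have the capability to make referrals". Consent and allocation take place at the home visit (Recruitment and enrolment; Randomization, allocation, and implementation), so the referral always precedes randomisation. Its day is not given.
- **Data source.** Table 2 marks PCP contact only under the Danish health registries, at Day 0 and again over follow-up. Data sources describes what the registers supply as consultations with the PCP.
- **Model.** Statistical analyses: "Univariate and multivariate logistic regression models will be used to compare secondary outcomes between the two groups".
- **Comparable outcomes.** Treatment changes are split into Outcome 8 (Day 0) and Outcome 9 (Day 1 to Day 30). Outcome 12 is not split.

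**The concern.** A count meant to show whether the intervention changes use of the PCP should contain events that allocation could change. Two kinds of Day 0 event could not be changed in this way: a PCP contact behind a same-day referral, which precedes randomisation, and the nurse's result call, which happens in both arms. Neither is excluded. If recorded, they form a block common to both arms that shrinks any ratio measure towards 1 and, where the block differs from patient to patient, adds noise.

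The model is a second, separate difficulty. Logistic regression needs a binary outcome, and Outcome 12 is a number of contacts. The obvious binary version, any contact against none, would be yes for nearly everyone if Day 0 events are recorded.

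**Working it through.** **The plan's own figure.** The article gives no contact rate, effect size or power for Outcome 12. Its only sample size is for the primary outcome: 31% against 21%, significance level 0.05, power 0.80. With a two-sided test and pooled variance this gives 300.8, so 301 per arm, as stated. I use 301 per arm below.

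**Assumptions (not in the article).**
- m = mean number of other contacts per control participant: 1, 2, 3 or 5.
- True rate ratio 0.80, Poisson counts.
- k = recorded contacts per participant that allocation cannot change: 0, 1 or 2.

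**Step 1: ratio.** Observed ratio = (0.80m + k)/(m + k). For m = 2, k = 1: (1.6 + 1)/(2 + 1) = 0.867.

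| m | k = 0 | k = 1 | k = 2 |
|---|---|---|---|
| 1 | 0.80 | 0.90 | 0.93 |
| 2 | 0.80 | 0.87 | 0.90 |
| 3 | 0.80 | 0.85 | 0.88 |
| 5 | 0.80 | 0.83 | 0.86 |

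**Step 2: difference in means, k the same for everyone.** The difference is (m + k) − (0.80m + k) = 0.20m, whatever k is. Its standard error is √((m + 0.80m)/301), also free of k. For m = 1: 0.20/√(1.8/301) = 2.59, so power = Φ(2.59 − 1.96) = 0.73. For m = 2 and 3, power is 0.955 and 0.994. A constant block costs nothing on this scale. On the log-ratio scale with robust errors, power is also kept (m = 1, k = 1: 0.737). With model-based Poisson errors it falls to 0.396, because the model overstates the variance.

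**Step 3: difference in means, k varying between patients (Poisson with mean k).** The standard error becomes √((m + 0.80m + 2k)/301).

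| m | power, k = 0 | k = 1 | k = 2 |
|---|---|---|---|
| 1 | 0.734 | 0.429 | 0.302 |
| 2 | 0.955 | 0.835 | 0.711 |
| 3 | 0.994 | 0.969 | 0.924 |
| 5 | 1.000 | 0.999 | 0.998 |

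**Step 4: any contact against none.** If every participant has one recorded Day 0 contact, both arms stand at 100% and no odds ratio can be estimated. With no such contacts (k = 0), the proportions are 1 − exp(−m) and 1 − exp(−0.80m).

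| m | control | intervention | power, any/none | power, count (step 2) |
|---|---|---|---|---|
| 1 | 63.2% | 55.1% | 0.529 | 0.734 |
| 2 | 86.5% | 79.8% | 0.588 | 0.955 |
| 3 | 95.0% | 90.9% | 0.502 | 0.994 |
| 5 | 99.3% | 98.2% | 0.247 | 1.000 |

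Moving the window alone therefore does not rescue a yes/no analysis. From about two contacts per person upwards it is already close to its ceiling and discards most of the information in the count.

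**The case against.** The strongest reply is that the article never says these contacts enter the data. Table 2 takes Outcome 12 from registries alone, and Data sources speaks of consultations; a nurse reporting results by telephone or electronic message is not evidently one. A reader might infer that Outcome 12 certainly contains the result call for every participant. The article does not support that: register handling is not described, and Study setting also names the hospital physician as a possible recipient. Nor does the referral contact always count. It must involve the PCP, and "Referrals are mainly made by PCPs" leaves other routes; it must also fall on the day of inclusion, which is not stated. This part of the reply stands, so the size is conditional.

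Second, Outcomes 1 and 4 also open at Day 0, and Outcome 9 starts at Day 1 only because Outcome 8 covers Day 0. That is fair. A Day 0 start is not wrong in itself, but the 8/9 pair shows a workable split.

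Third, one might infer that the comparison is diluted on every scale. Step 2 shows that it is not.

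Fourth, the any/none ceiling might be blamed on the Day 0 window. Step 4 shows that it largely remains without Day 0 contacts, and the article does not say the count will be dichotomised. The model mismatch is thus a separate point.

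Fifth, a journal article may leave the definition of a contact to a fuller document. That is accepted for the definition. The window and the model, however, are stated here, and the stated model does not suit the stated outcome.

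**Conclusion.** The point holds in a limited, conditional form. Outcome 12 opens on the calendar day of inclusion and excludes neither a same-day contact before randomisation nor the nurse's result call. If the registers record these, a true rate ratio of 0.80 would appear as about 0.83 to 0.93, given 1 to 2 such contacts and assumed means of 1 to 5 others. Precision also falls if they vary between patients, most where contacts are few (power 0.734 to 0.429 or 0.302 at a mean of 1). These sizes rest on assumed rates, an assumed effect and Poisson counts. Independently of the registers, logistic regression does not fit a count. The consequence is confined to one secondary outcome, favours neither arm and leaves the primary outcome untouched. It is a cheap improvement to make before analysis.

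**What to change.** 1. State which register entries count as a PCP contact, and exclude the referral contact and the nurse's result call.
2. Report and compare Day 0 and Day 1 to Day 30 contacts separately, following Outcomes 8 and 9. If the register cannot identify the two excluded events, the Day 1 to Day 30 count still leaves out those dated Day 0.
3. Analyse the number of contacts with a count model, such as negative binomial or Poisson with robust errors, in place of logistic regression.

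**Cost.** The wording of one outcome and its model change. No new data are needed, since Table 2 already takes registry data for both periods. The drawback is that genuine contacts after the visit on Day 0, such as a same-day consultation prompted by the results, fall outside the Day 1 to Day 30 count. Allocation could affect these, so Day 0 should keep its own comparison between arms and not be reduced to description.
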